## Abstract

**ABSTRACT:**

**Introduction:**

Nigeria has the highest number of maternal deaths globally, and maternal peripartum sepsis is one of the leading causes of maternal mortality. A single oral dose of azithromycin (AZM; 2 g) is safe and effectively reduces 33%–60% of maternal sepsis during planned vaginal birth in low- and middle-income countries (LMICs). However, the clinical and cost-effectiveness of oral AZM during vaginal birth in Nigeria remains unknown in the context of poor antimicrobial stewardship practices, significant antimicrobial resistance and healthcare financing. Evidence is also lacking on the standard care for the prevention of maternal sepsis among pregnant women undergoing vaginal births in Nigeria. The AZIN-V trial is a hybrid type 2 effectiveness-implementation trial to determine the safety, clinical and cost-effectiveness of intrapartum oral AZM versus usual care in the prevention of peripartum maternal sepsis. The trial will also examine the impact of implementation strategies in enhancing adherence to the oral AZM protocol during planned vaginal births and identify effective strategies to improve adherence (fidelity) to the protocol in real-world LMIC settings.

**Methods and analysis:**

This is a multicentre hybrid type 2 trial conducted in six Nigerian states: Ebonyi, Edo, Gombe, Kano, Kwara and Lagos. The study aims to simultaneously test the clinical and cost-effectiveness of AZM (clinical trial) and the impact of implementation strategies (implementation research) in Nigeria’s unique healthcare context. The clinical trial is a two-arm, cluster-randomised controlled trial conducted across 48 health facilities, randomly assigned (1:1) to either intrapartum administration of oral AZM (intervention group) or usual care—the current routine practice (control group). A total of 5040 study participants (2520 in each group) will be enrolled in the clinical trial. The implementation trial is a two-arm cluster non-randomised controlled trial conducted in 12 health facilities (1:1) allocated to either a bottom-up approach using the Plan-Do-Study-Act cycle or a usual top-down approach with a one-time training workshop and distribution of clinical guidelines, with both arms administering oral AZM during vaginal birth while assessing fidelity (primary outcome).

For the clinical trial, data will be analysed using intention-to-treat statistical methods. The cost-effectiveness outcome will be analysed using the Incremental Cost-Effectiveness Ratio. Implementation outcomes will be analysed using descriptive statistics and a thematic approach.

**Ethics and dissemination:**

This study has been approved by the National Health Research Ethics Committee, Nigeria (NHREC/01/01/2007-30/09/2024), the ethics committees of the participating health institutions (Lagos University Teaching Hospital Research Ethics Committee: ADM/DSCST/HREC/APP/6325; University of Ilorin Teaching Hospital Health Research Ethics Committee: ERC/PAN/2025/03/0581; University of Benin Teaching Hospital Health Research Ethics Committee: ADM/E22/A/VOL. VII/483117141; Aminu Kano Teaching Hospital Research Ethics Committee: AKTH/MAC/SUB/12 A/P-3/VI/2509 and Irrua Specialist Teaching Hospital Research Ethics Committee: ISTH/HREC/20241507/605), the Ministries of Health of the six states and the National Agency for Food and Drug Administration and Control. Written informed consent will be obtained from all eligible study participants before enrolment. Results will be shared with communities and policy stakeholders and through peer-reviewed journals and will be presented at conferences.

**Trial registration number:**

ISRCTN16415327.

STRENGTHS AND LIMITATIONS OF THIS STUDYThis is a cluster-randomised clinical and cost-effectiveness trial of the intrapartum use of 2 g oral azithromycin (AZM) to prevent maternal sepsis among pregnant women undergoing vaginal birth in Nigeria, a country that accounts for 29% of all global maternal deaths.The trial will be conducted across six Nigerian states, one state selected from each of the country’s geopolitical zones and from different levels of healthcare delivery, which will ensure diversity and generalisability of the trial results.This trial represents a systematic evaluation of Plan-Do-Study-Act cycles for developing context-specific implementation strategies to enhance skilled health personnel’s adherence to intrapartum AZM protocols and could inform effective adoption and implementation in other comparable resource-constrained settings across Africa and beyond.As an open-label, cluster-design clinical trial, the participating sites were informed of their allocation, and this awareness may influence the clinical management practices or reporting behaviours across sites.The definition of usual care is not standardised across participating health facilities (study sites), and variations in routine practices for maternal sepsis prevention may introduce heterogeneity in the comparator arm.

## Introduction

 Maternal morbidity and mortality due to complications arising during pregnancy and childbirth remain a global health concern.^1^ Globally, an estimated 287 000 maternal deaths occurred in 2020, around 70% of which were in sub-Saharan Africa (SSA).^2^ Nigeria, the most populous country in SSA, bears the highest burden, accounting for nearly 29% of global maternal deaths,^2^ with peripartum sepsis as one of the leading causes.^3^,^6^ Maternal peripartum sepsis accounts for around 11% of all global maternal deaths, with a disproportionately higher burden in low- and middle-income countries (LMICs; 10%) compared with 5% in high-income countries.^1 7^ Maternal sepsis accounts for 17.3%–20.6% of maternal deaths in tertiary hospitals in Nigeria.^3 8^

To reduce maternal deaths from sepsis, the WHO recommends the use of antibiotics around birth to prevent and treat maternal peripartum infection in some clinical situations, including caesarean sections and operative vaginal births.^9 10^ Azithromycin (AZM), an inexpensive, heat-stable, orally administered broad-spectrum macrolide antibiotic with a prolonged half-life, is effective against Gram-positive and Gram-negative bacteria,^11^,^13^ responsible for maternal sepsis in SSA.^14^,^19^ While prophylactic use of antibiotics for caesarean birth is well-established and highly recommended,^20^,^22^ researchers continue to explore the clinical usefulness of intrapartum AZM in the prevention of maternal sepsis during vaginal birth.^23^,^25^ A single 2 g dose of AZM given orally is safe and cost-effective and has been shown to reduce maternal sepsis or death by 33%–60% during vaginal birth in LMICs, including SSA.^2324 26^,^28^

Although AZM has shown benefits in preventing maternal sepsis during vaginal births in other sub-Saharan African countries, several factors necessitate Nigerian-specific evidence before policy adoption. Nigeria’s distinctive antimicrobial resistance landscape, characterised by high resistance rates (up to 40% for Enterobacteriaceae and *Staphylococcus aureus*,^29 30^ the predominant causative organisms for maternal sepsis in SSA^31^) and high antibiotic exposure during pregnancy (due to antenatal infections and injudicious use of antibiotics), may reduce AZM’s effectiveness against most bacterial isolates responsible for maternal sepsis compared with previous trial settings.^32^,^34^ Additionally, Nigeria’s healthcare infrastructure varies considerably from primary health centres with limited laboratory capacity to tertiary hospitals with advanced diagnostic capabilities, potentially affecting both sepsis recognition and AZM’s clinical impact, while the economic implications of routine AZM use differ substantially in Nigeria’s healthcare financing context, where out-of-pocket payments constitute over 70% of health expenditures.^35^ A large randomised controlled trial is needed in Nigeria to assess the effectiveness and cost-effectiveness of a single dose of oral AZM during vaginal birth to reduce maternal sepsis and to guide clinical practice in Nigeria.

Beyond evidence on its effectiveness, there are also knowledge gaps regarding implementation. From an implementation perspective, the effective deployment of oral AZM for the prevention of maternal sepsis requires skilled health personnel’s (SHP’s) adherence to protocols in healthcare facilities.^36 37^ However, the typical top-down approach in Nigeria for guidelines or policy changes is to conduct a one-off training workshop and distribute the guidelines.^38^ This approach lacks evidence of sustained provider compliance, and no study has systematically evaluated implementation strategies to enhance SHP’s adherence to intrapartum AZM protocols in sub-Saharan settings. In addition, there is limited evidence on the facilitators, barriers and contextual factors influencing the implementation of oral AZM during vaginal birth to inform the design of context-specific implementation strategies and improve adherence.^23^ The Plan-Do-Study-Act (PDSA) cycle, a bottom-up approach, offers a promising strategy to develop, test and refine context-specific implementation strategies for the effective integration of evidence-based interventions, like intrapartum AZM prophylaxis, into routine practice in LMICs.^39^,^41^ Given the absence of AZM adoption in Nigeria for the prevention of maternal sepsis and uncertainty about effective implementation strategies,^42^ a systematic comparison of PDSA-generated strategies versus the usual strategy is needed to improve the fidelity of oral AZM in practice while upholding ethical standards and strategies to enhance SHP’s adherence across Nigeria’s health system and respecting the local medical context.

The AZIN-V trial is a hybrid type 2 effectiveness-implementation trial that simultaneously tests the clinical and cost-effectiveness of AZM while evaluating implementation. This study represents, to our knowledge, the first systematic evaluation of PDSA cycles for developing context-specific implementation strategies to enhance SHP’s adherence to intrapartum AZM protocols and would inform effective adoption and implementation in other comparable resource-constrained settings across Africa and beyond.

### Objectives

To assess the clinical effectiveness and safety of intrapartum administration of oral AZM compared with the current routine health-facility practice (usual care) for the prevention of maternal sepsis among pregnant women undergoing vaginal birth across multiple health facilities in Nigeria.To estimate the incremental costs and cost-effectiveness of oral AZM compared with the current standard of care in preventing maternal sepsis among women undergoing vaginal birth across multiple health facilities in Nigeria.To assess the effectiveness of SHP-tailored strategies to enhance the fidelity of oral AZM as part of a sepsis prevention protocol during vaginal birth across multiple health facilities in Nigeria.

## Methods and analysis

### Study design

This protocol is reported in line with the Standard Protocol Items: Recommendations for Interventional Trials 2025 reporting guidelines.^43^

This is a hybrid type 2 effectiveness-implementation study.^44 45^ It comprises two components: (1) an intervention study to assess the effectiveness of oral AZM use in labour to prevent maternal sepsis among pregnant women undergoing vaginal birth and (2) implementation research to evaluate the implementation process (figure 1). AZIN-V includes two cluster-design parallel-group trials: a safety and effectiveness randomised trial conducted across 48 health facilities and an implementation trial conducted in 12 facilities.

**Figure 1 F1:**
[figure not shown]
Trial flow diagram. PDSA, Plan-Do-Study-Act.

### Study setting

The study is conducted across six Nigerian states, one state selected from each of the country’s geopolitical zones to ensure broad coverage: Ebonyi, Edo, Gombe, Kano, Kwara and Lagos. These states were selected based on differences in maternal healthcare indices and health system characteristics between the northern and southern regions. Study sites will include primary, secondary or tertiary health facilities that are either public or private. The list of study sites can be obtained from the trial registry (ISRCTN16415327).

### Sites

From the six states, 48 health facilities are included in the clinical trial. The implementation trial will include 12 health facilities from the six states. Sites will only participate in either the clinical or the implementation trial. Study sites are selected based on their state-level location to avoid serving the same geographic clusters or communities, thereby reducing the risk of cluster contamination. The selection process will ensure a within-state comparison across various levels of healthcare (primary, secondary and tertiary) and facility types: public (government-owned) and private.

### Clinical trial

#### Eligibility criteria

##### Sites

For sites to be eligible for either the clinical trial or implementation trial, they must have an antenatal clinic that serves at least 50 pregnant women per month and a labour ward that offers 24-hour vaginal birth services with an average of 20 vaginal births per month. Data were based on health facility records at potential study sites.All selected study sites will sign a trial agreement before randomisation to commit to the assigned intervention group after randomisation. Thereafter, each study site is assigned a unique code for identification.

##### Participant inclusion criteria

Pregnant women with a live or stillborn singleton or twin pregnancy of at least 24+0 weeks’ gestation in the active phase of the first stage of labour (cervical dilatation of 4 cm or more) or the early (non-pushing) phase of the second stage of labour.Pregnant women admitted in labour to the selected health facilities following spontaneous or induced labour with a planned vaginal birth.

##### Participant exclusion criteria

Pregnant women of gestational age <24 weeks.Pregnant women who are not admitted to the facility with a plan to deliver vaginally.Pregnant women in threatened preterm labour with no immediate plan for birth.Pregnant women with a fever >38°C.Pregnant women with a history of use of a macrolide antibiotic in the previous 3 days.Pregnant women with a known allergy to AZM, its excipients or other macrolide antibiotics.Pregnant women with a known history of cardiac disease (such as cardiac arrhythmia or cardiomyopathy).Pregnant women with a planned caesarean birth.

### Intervention

For the clinical trial, a single 2 g oral dose of AZM will be administered to eligible participants in intervention sites. All other aspects of usual care in the health facility will remain the same (eg, handwashing, use of hand gloves and aseptic techniques). After obtaining written informed consent from an eligible participant, the health worker attending the birth will administer the oral AZM as a directly observed therapy.

### Control

Participants in control sites will receive usual routine care, as described above. AZM will not be provided to the control sites.

### Adherence and participant follow-up

After the potential participant has read the participant information sheet and consent form, but before she signs, the research staff will show her a sample study drug and confirm verbally that she is willing and able to take the AZM as prescribed (four 500 mg capsules) as part of the written informed process. Only if she is willing to commit to taking the pill and agrees to the scheduled follow-up visits will she be enrolled in the study after signing the consent form; otherwise, this is recorded as unwilling to give consent. Research nurses will witness the study participants taking the study drug. All participants (at intervention and control sites) will be followed up until discharge, with surveillance maintained (virtually and in person), and visits at 3 days, then at 2, 4 and 6 weeks after birth. Adherence will be monitored by the trial management group (TMG).

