### Randomisation

Sites were randomly assigned in a 1:1 ratio to either the intervention group or the control group. Randomisation was based on a minimisation algorithm that considered the state, facility level (primary, secondary and tertiary) and empirical postpartum use of antibiotics. Randomisation was undertaken by the statisticians, and the health facilities were informed of their random allocation before any participants were assessed for eligibility.

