### Statistical methods and analysis

All analyses will be intention-to-treat unless specified. Categorical variables will be summarised as frequencies and percentages. Continuous variables will be presented with N (number of observations), means (SD) and/or medians (IQRs), depending on whether they are normally distributed. The primary outcome will be analysed using a random effects logistic regression model to estimate the treatment effect with 95% CI. The model will be adjusted for the stratification variables, along with any imbalance in key baseline variables. The secondary outcomes will be analysed using random-effects models depending on the distribution of the outcome. Missing data will be described explicitly with the number reported for each variable, and where appropriate, multiple imputation methods may be employed. An interim analysis will be conducted at the halfway point through the trial (50% of the target sample with the primary outcome). If the p value indicates an overwhelming effect (as evidenced by a p value less than 0.001—the Haybittle-Peto rule),^49^ the DSMB may request unblinding, and a recommendation to stop the trial may be considered.

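### Enrolment requires commitment to capsules that only one arm gives, after sites know their allocation, so the intention-to-treat set may be selected differently in the two arms

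*Protocol article*

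**What the plan says.** The Randomisation section states that "the health facilities were informed of their random allocation before any participants were assessed for eligibility", and the Blinding section confirms that sites are not blinded. The Intervention section gives the single oral dose at intervention sites, after written consent. The Control section says "AZM will not be provided to the control sites".

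The entry condition is in Adherence and participant follow-up, not in the lists of participant criteria. As a step ahead of signature, "the research staff will show her a sample study drug and confirm verbally that she is willing and able to take the AZM as prescribed". The rule that this leads to is: "Only if she is willing to commit to taking the pill and agrees to the scheduled follow-up visits will she be enrolled". For a woman who does not meet it, "otherwise, this is recorded as unwilling to give consent". Later in the same paragraph, "Research nurses will witness the study participants taking the study drug".

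The Statistical methods and analysis section then says "All analyses will be intention-to-treat unless specified".

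**The concern.** In a cluster trial that recruits after open allocation, the randomised comparison is safe only if the same kind of woman enters in both arms. Here entry depends on willingness and ability to take a treatment that one arm gives and the other does not.

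The follow-up sentence in that section is expressly extended to intervention and control sites. The capsule check speaks only of the potential participant, so its scope is open. On one reading it runs only where AZM is given, and women drop out of one arm. On the other, control women are asked to commit to capsules that their site will not supply. That question does not carry the same weight and may not screen out the same women.

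A woman screened out before signing has no outcome data. Intention-to-treat analysis, the random-effects model and multiple imputation all work on enrolled women, so none of them brings her back.

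**Working it through.** **Inputs from the Sample size section.** Risk 6.5% against 3.25%, power 90%, level 5% (taken as two-sided), ICC 0.011, 20% loss, 48 facilities of about 105 women.

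**The plan's own figure.** Two proportions without clustering: 921 per arm. Design effect 1 + (105 − 1) × 0.011 = 2.144, giving 921 × 2.144 = 1975. Allowing for loss: 1975 / 0.80 = 2469 per arm, 4938 in all. That is 2.0% below the stated 5040, and 48 × 105 = 5040 exactly. The sample size reproduces and is not in question.

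**Precision for the illustration.** Evaluable women per facility: 105 × 0.80 = 84. Design effect 1 + 83 × 0.011 = 1.913. Effective number per arm: 24 × 84 / 1.913 = 1054.

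**Assumptions not in the document.** AZM has no effect. Overall risk is 6.5% in both arms. A share x of otherwise eligible AZM-site women fails the check, with k times the risk of those who pass. No control-site woman is filtered.

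**Formulas.**
- Risk among enrolled AZM-arm women: p = 0.065 / (1 − x + xk). The risk ratio is p / 0.065.
- Standard error of the difference: √[(0.065 × 0.935 + p(1 − p)) / 1054].
- Probability of a significant result in favour of AZM: Φ[(0.065 − p)/SE − 1.96]. It is 2.5% when there is no bias.

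| x | k | p | Risk ratio | Probability of false benefit |
|---|---|---|---|---|
| 5% | 2 | 6.19% | 0.95 | 4.8% |
| 10% | 2 | 5.91% | 0.91 | 8.1% |
| 15% | 2 | 5.65% | 0.87 | 12.6% |
| 20% | 2 | 5.42% | 0.83 | 18.2% |
| any | 1 | 6.50% | 1.00 | 2.5% |
| 20% | 0.5 | 7.22% | 1.11 | 0.4% |

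Worked row (x = 10%, k = 2): p = 0.065 / 1.10 = 0.0591; SE = 0.0105; (0.065 − 0.0591)/0.0105 = 0.56; Φ(0.56 − 1.96) = 0.081.

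**If control women are asked but fewer decline.** Suppose 20% of women would fail a real check at twice the risk, and the hypothetical question removes only a quarter of them (5% of all women) at control sites. Acceptors' risk is 0.065 / 1.20 = 0.0542. Control-arm risk is 0.0542 × (0.80 + 0.15 × 2) / 0.95 = 0.0627. The risk ratio is 0.0542 / 0.0627 = 0.86 and the probability of false benefit is about 13%. If the check removes the same women in both arms, the ratio is 1.

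**Returning decliners at control-arm risk.** With k = 2, the AZM-arm risk becomes (1 − x)p + 0.065x. The risk ratio moves from 0.909 to 0.918 (x = 10%), 0.870 to 0.889 (15%) and 0.833 to 0.867 (20%). Most of the bias stays, so that single assumption is not an adequate sensitivity analysis.

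**The case against.** A reader might infer that decliners leave the AZM arm but not the control arm. The document does not establish this. The check is described for the potential participant without limit of arm, and withholding AZM from control sites governs treatment, not the consent conversation. This part of the objection stands: one-arm filtering is one of two readings.

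A reader might also infer that women who fail to take the drug drop out of the analysis. That is not supported. Consent and enrolment come before directly observed dosing, and no section removes a woman who signs and then does not take it. Only women unwilling or unable before signing are lost.

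Other exclusions already act in both arms: fever, macrolide allergy, cardiac disease, and consent required before the pushing phase. They shrink the group of ill or late-presenting women whom the capsule check could remove, and the document gives no evidence that those left are at higher risk of sepsis. The decliner shares and risks used above are therefore assumptions, and the sign of the bias is open.

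Finally, the primary model adjusts for the stratification variables and for imbalance in key baseline variables. That helps with measured differences between enrolled women but cannot remove unmeasured selection.

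What remains is that the text states an entry rule tied to one arm's treatment, applied after open allocation, and contains nothing to secure equal filtering. This is a stated rule, not a detail left to the analysis plan.

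**Conclusion.** The point holds as a possible selection bias in the primary comparison, not as a demonstrated one-arm exclusion. On either reading, the intention-to-treat set is formed after sites know their arm, by a criterion whose practical meaning differs between arms.

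Direction and size cannot be fixed from the document. The range of about 0.91–0.83 for the risk ratio, with 8–18% probability of false benefit, rests on one-arm filtering of 10–20% of women at twice the acceptors' risk and no drug effect. There is no bias if decliners have equal risk or if the same women are removed in both arms. The risk ratio rises to about 1.11 if 20% are removed at half the risk.

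**What to change.** 1. Reconcile the Intervention, Control, Adherence and participant follow-up, and Randomisation sections, and state what control-site women have been asked so far.
2. For the remaining recruitment, use one enrolment rule in both arms: consent to data collection and follow-up, without commitment to the pill as a condition of entry.
3. State that every enrolled woman is analysed in her site's arm whether or not she took AZM.
4. For women already screened, use the existing record of unwilling women to report eligible, declined (with reason) and enrolled women by arm and site. Refusal of the pill and refusal of the visits appear to share one label, so past reasons may be only partly recoverable.
5. Prespecify a sensitivity analysis that returns decliners over a range of assumed risks below and above control-arm risk, not at control-arm risk alone.

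The cost is a short amendment to the consent script, a table and one analysis. Enrolling some women who do not take the drug slightly dilutes the intention-to-treat effect. The new rule will reach few women, because the Trial status section projects recruitment to end by March 2026, and AZM-site entry will differ before and after the change. For most of the trial, items 3 to 5 therefore carry the remedy.
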